### Statistical Analysis

For the primary outcome, linear mixed effects models will be used to compare changes from baseline home BP to 6 months from enrollment between the integrated and nonintegrated remote monitoring arms of the study. Models will include random site effects to account for the clustering of patients within sites. Models will adjust for demographic and clinical characteristics including age, sex, race, and ethnicity, as well as social vulnerability (the census tract Social Vulnerability Index). The evaluation of each arm will be based on a Wald test of the primary model term, and estimated differential changes will be reported along with a 95% CI. For the dichotomous secondary outcomes, we will use mixed effects logistic regression models with similar specifications and report differences in terms of odds ratios. A significance level of .05 will be used, and all analyses will follow the intention-to-treat principle. For patients who do not have a BP reading at 6 months, we will use the reading closest to 6 months, with a minimum 2-month period between the baseline and final reading [23,24]. Missing data will be handled through multiple imputations using pattern-mixture models. For the exploratory pre-post analysis, we will use linear mixed effects models to evaluate changes in BP. The analysis will be performed using SAS (version 9.4; SAS Institute Inc).

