**Methods:**

We will conduct a randomized, comparative effectiveness trial at 3 large academic health centers across California. The 3 sites will enroll a total of 660 participants (approximately n=220 per site), with 330 in the integrated BP monitor arm and 330 in the nonintegrated BP control arm. The primary outcome of this study will be the absolute difference in systolic BP in mm Hg from enrollment to 6 months. Secondary outcome measures include binary measures of hypertension (controlled vs uncontrolled), hypertension-related health complications, hospitalizations, and death. The list of possible participants will be generated from a central data warehouse. Randomization will occur after enrollment in the study. Participants will use their assigned BP monitor and join site-specific hypertension interventions. Cross-site learning will occur at regular all-site meetings facilitated by the University of California, Los Angeles Value-Based Care Research Consortium. A pre- and poststudy questionnaire will be conducted to further evaluate participants’ perspectives regarding their BP monitor. Linear mixed effects models will be used to compare the primary outcome measure between study arms. Mixed effects logistic regression models will be used to compare secondary outcome measures between study arms.

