### Enrollment, Randomization, and Study Initiation

Figure 2 describes the study phases, starting with the creation of the potential participant list obtained from the Center for Data-Driven Insights and Innovation (CDi2) and the UC Health Data Warehouse (UCHDW), verification of eligibility criteria, and study enrollment, which we aim to start in the second quarter of 2023. This study plans to enroll 660 participants (about 220 per site and 330 participants in each arm of the study). These power calculation estimates are based on previous literature reviews [18,19] to achieve an 80% power to detect a difference of 0.23 SDs and an anticipated 10% attrition rate. An enrollment script will be provided to each site (Multimedia Appendix 2). Randomization will occur after enrollment using a randomization allocation template within REDCap (Research Electronic Data Capture), a secure web-based platform designed to help capture data and operationalize research studies [20,21].

After enrollment and randomization, participants will receive their BP monitor (integrated or nonintegrated) and complete a prestudy questionnaire (Multimedia Appendix 3). Each UC site will then administer their site-specific hypertension intervention, which will be administered to both arms of the study. At the end of the 6-month follow-up period, a similar poststudy questionnaire evaluating participant experiences will be completed (Multimedia Appendix 4). Given the nature of the different BP management interventions, site representatives and participants will not be blinded to study arm assignments; however, the UCLA VBCRC evaluation team will be blinded.

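### The primary comparison of BP changes does not name baseline BP as a covariate, which gives up precision, although the stated 80% power is not shown to be missed

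*Protocol article*

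**What the plan says.** The abstract sets the outcome: "The primary outcome of this study will be the absolute difference in systolic BP in mm Hg from enrollment to 6 months". The Statistical Analysis section sets the method: "linear mixed effects models will be used to compare changes from baseline home BP to 6 months from enrollment". On covariates it says: "Models will adjust for demographic and clinical characteristics including age, sex, race, and ethnicity, as well as social vulnerability". The social vulnerability measure is a census-tract index. Clinical characteristics are promised, but none is listed, and baseline BP is not mentioned as a covariate anywhere in the article.

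On site and testing the section adds "Models will include random site effects to account for the clustering of patients within sites" and "The evaluation of each arm will be based on a Wald test of the primary model term, and estimated differential changes will be reported". The binary secondary outcomes, including hypertension control, are to be modelled along similar lines.

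The sample-size text, under Enrollment, Randomization, and Study Initiation, reads "This study plans to enroll 660 participants (about 220 per site and 330 participants in each arm of the study", chosen "to achieve an 80% power to detect a difference of 0.23 SDs and an anticipated 10% attrition rate". It does not say whether the SD is that of the BP level or of the change, and it gives no correlation between baseline and 6 months.

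**The concern.** Baseline BP is normally among the strongest predictors of later BP. Subtracting it fixes its coefficient at 1, whereas entering it as a covariate lets the data estimate the coefficient. When the correlation is moderate, a coefficient of 1 over-corrects, and the change score carries avoidable noise, including the effect of any chance imbalance at baseline. At stake are the width of the confidence interval for the primary contrast and the chance of detecting a real but modest difference between two arms that receive the same site programme. The hypertension-control model would inherit the same gap, although starting BP has much to do with who falls below 130/80 mm Hg.

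The unidentified SD adds to this. An effect of 0.23 SD of the level and one of 0.23 SD of the change differ in mm Hg unless r is 0.5, so the reader cannot tell what effect the trial is sized for.

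**Working it through.** **Inputs from the article.** Effect 0.23 SD, power 80%, significance level .05, attrition 10%, 330 enrolled per arm. Sidedness is not stated; two-sided is used because it reproduces the planned size.

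**Assumptions, not in the article.** Equal variances at baseline and 6 months; correlation r shown from 0.3 to 0.7; the covariate is the same baseline measure used to form the change.

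**Reproducing the plan.** n per arm = 2(1.96 + 0.8416)² / 0.23² = 296.7, so 297. Allowing for attrition, 297 / 0.9 = 330 per arm, or 660 in total. This matches exactly. A one-sided test would give 260 per arm, which does not match. The calculation is a plain two-sample comparison in SDs of whatever variable is analysed.

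**Variances, with the SD of the BP level set to 1.**
- Change score: 2(1 − r)
- Baseline-adjusted: 1 − r²
- Ratio, adjusted to change: (1 − r²) / [2(1 − r)] = (1 + r)/2, which is below 1 for every r below 1

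**Power at 297 analysed per arm** = Φ(d√(297/2) − 1.96), where:
- Reading A (0.23 in SDs of the level): d = 0.23/√[2(1 − r)] for change, 0.23/√(1 − r²) adjusted
- Reading B (0.23 in SDs of the change): d = 0.23 for change, 0.23/√[(1 + r)/2] adjusted

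| r | Variance cut by adjusting | A: change | A: adjusted | B: change | B: adjusted |
|---|---|---|---|---|---|
| 0.3 | 35% | 65.9% | 83.6% | 80.0% | 93.5% |
| 0.4 | 30% | 72.5% | 86.4% | 80.0% | 91.8% |
| 0.5 | 25% | 80.0% | 89.9% | 80.0% | 89.9% |
| 0.6 | 20% | 88.0% | 93.9% | 80.0% | 88.0% |
| 0.7 | 15% | 95.1% | 97.5% | 80.0% | 86.0% |

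Example, reading A at r = 0.3: d = 0.23/√1.4 = 0.194; 0.194 × √148.5 = 2.369; Φ(2.369 − 1.96) = 65.9%.

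**In participants.** At r = 0.5 the adjusted analysis needs 496 enrolled for 80% power, against 660 for the change score. Under reading A the change score would need 926 at r = 0.3 and 794 at r = 0.4.

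**What the table shows.** Adjustment helps in every row under both readings. The unadjusted change score falls below 80% only under reading A with r below 0.5.

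**The case against.** The strongest reply is that the covariate list is open. It is introduced by *including*, it promises clinical variables without listing any, and the article condenses a fuller protocol, so baseline BP may be specified there. Reporting differential changes also fits a repeated-measures model with a common baseline mean, which is about as efficient as baseline adjustment. This stands as a limit: the article does not rule out an efficient model. But it does name the model class, the random site effect, the test and the covariates down to a census-tract index, and what it describes fits the inefficient forms equally well.

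A reader might infer that the trial misses its 80% power. The documents do not support that. The 660 reproduces, the stated primary outcome is the change, and if the SD is that of the change, power is 80% whatever r is. A shortfall needs two things the article does not give: the level SD and r below 0.5. Nor can a low r be presumed because participants are selected for high BP. Eligibility rests on earlier readings tied to outpatient visits, whereas the model uses baseline home BP, so any truncation is indirect and of unknown size.

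A reader might also infer that regression to the mean biases the contrast. It does not: in expectation it is the same in both randomised arms and cancels, leaving only chance imbalance, which is a matter of precision.

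One practical objection stands. Monitors are received after enrollment and randomization, so a baseline taken on the study device appears to be post-randomisation. A reading that is certainly pre-randomisation would probably come from the EHR and may correlate less with 6-month home BP. The gains in the table would then be smaller.

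**Conclusion.** The point holds as one of efficiency and specification. As described, the primary analysis compares changes without naming baseline BP, and an unadjusted change score or an arm-by-time model with unconstrained baseline means is less precise than a baseline-adjusted one for any r below 1. The variance saving is 35% at r = 0.3, 25% at 0.5 and 15% at 0.7. If 0.23 is in SDs of the change, power rises from 80% to 93.5%, 89.9% and 86.0% respectively. These figures rest on equal variances, an assumed r, and adjustment for the same measure that forms the change.

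No power shortfall is demonstrated. It remains a conditional possibility (66% at r = 0.3 and 73% at r = 0.4 under the level reading; 80% or more from r = 0.5 upward) that the article cannot exclude, because it does not say which SD is meant.

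**What to change.** - **Primary model.** State it as 6-month systolic BP (or its change) on arm, with baseline systolic BP as a covariate, plus site and the covariates already listed.
- **Which baseline.** Use the reading from which the change is computed if it is taken before care can differ between arms. Otherwise use the pre-randomisation systolic BP in the EHR that qualified the participant, and accept that the gain may be smaller. Say which is used.
- **Hypertension control.** Add baseline BP to the logistic model.
- **Sample-size text.** Say whether 0.23 is in SDs of the BP level or of the change. If it is the level, give the assumed correlation.

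The cost is a few lines of model and sample-size wording, with no new visits, data or participants. The change should be made before any unblinded analysis.

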### Site-Specific Hypertension Interventions

In addition to following core protocol instructions, each site will design and implement a hypertension intervention for both arms of the study. The study sites are given the autonomy to create their own site-specific hypertension intervention to fit their patient population needs and available resources. Table 1 compares interventions across each UC site, including whether the intervention is web-based only or hybrid (component of in-person and web-based), the main health care providers involved in the intervention, specific details about the intervention, discharge criteria from the program, and site-specific inclusions and exclusions.

**Table 1 table1:** Comparison of site interventions.

	University of California, Davis	University of California, Los Angeles	University of California, San Francisco
Web-based only, hybrid (in-person and web-based)	Hybrid	Web-based only	Hybrid
BP^a^ monitor distribution plan (eg, mail, in person, etc)	Mailed directly to the patient	Mailed directly to the patient	Mailed directly to the patient
Main providers involved in the intervention	Pharmacist	Pharmacist Patient service representative Primary care provider Program supervising physician	Pharmacist Primary care provider Health care navigator
General structure of study arms	Intervention: EHR^b^ integrated remote BP monitor with pharmacist follow up Control: nonintegrated BP monitor with pharmacist follow up	Intervention: EHR integrated remote BP monitor + web-based patient portal Control: nonintegrated BP monitor + web-based patient portal	Intervention: EHR integrated remote BP monitor + usual care and follow-up Control: nonintegrated BP monitor + usual care and follow-up
Frequency of BP checks	There is no minimum per month. Ideally, at least 16 per month.	There is no minimum per month. Ideally, at least 16 per month.	There is no minimum per month; however, patients will receive daily reminders. Ideally, at least 16 per month.

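### The 6-month primary value is worded as one home reading per participant although ideally 16 or more a month are sought, so avoidable reading noise enters the change score and the control status

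*Protocol article*

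**What the plan says.** The abstract of the Protocol article defines the primary outcome: "The primary outcome of this study will be the absolute difference in systolic BP in mm Hg from enrollment to 6 months". The Statistical Analysis section says the linear mixed model will "compare changes from baseline home BP to 6 months from enrollment between the integrated and nonintegrated remote monitoring arms". For the month-6 value it gives a selection rule: "For patients who do not have a BP reading at 6 months, we will use the reading closest to 6 months". The same section requires this value to fall at least 2 months after baseline. Each reference is to a single reading. The only random effect named is site, so the stated model has no participant-level term that could use repeated readings. Averaging is not mentioned anywhere in the article.

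Table 1 (Site-Specific Hypertension Interventions) sets no minimum number of readings per month but adds, at all three sites, "Ideally, at least 16 per month". The section on monitors and EHR integration says that integrated readings reach the EHR automatically, while the other arm reports its own readings through the patient portal.

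The secondary control status is a dichotomy at 130 mm Hg systolic or 80 mm Hg diastolic (Primary and Secondary Outcomes).

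The sample size statement reads "This study plans to enroll 660 participants (about 220 per site and 330 participants in each arm of the study", chosen "to achieve an 80% power to detect a difference of 0.23 SDs and an anticipated 10% attrition rate".

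**The concern.** A single home reading is the person's current level plus short-term noise. Where several readings near month 6 exist, taking one discards information that is already collected. The noise widens the SD of the primary change score and so lowers power for a given effect in mm Hg. It also misclassifies control status for participants whose usual level lies near the threshold.

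The article does not merely leave this open: it states a rule, and the rule selects one value. At stake is the precision of the primary comparison, in a trial planned with no more than 80% power.

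**Working it through.** **1. The plan's own figure.** Inputs from the article: difference 0.23 SD, power 80%, attrition 10%, and "A significance level of .05 will be used". Sidedness is not stated; two-sided is assumed.

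- n per arm = 2(1.960 + 0.842)² / 0.23² = 296.7, so 297.
- 297 / 0.90 = 330 per arm, 660 in total. This matches exactly. (One-sided would need 234 per arm before attrition and does not match.)
- Power at 297 per arm = Φ(0.23 × √(297/2) − 1.960) = 80.0%.

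**2. Model for the change score.** The documents give neither an SD in mm Hg nor a within-person variance, so these are assumptions: between-person SD 12 at each time, within-person (reading) SD s = 8 or 10, true baseline-to-month-6 correlation ρ = 0.3 or 0.5, and independent readings. The planned 0.23 SD is taken to refer to the change between two single readings.

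- Single readings at both times: V₁ = 2 × 144 × (1 − ρ) + 2s².
- Month 6 averaged over k readings, baseline single: V = 2 × 144 × (1 − ρ) + s² + s²/k.
- Power for the same mm Hg effect = Φ(0.23 × √(V₁/V) × √(297/2) − 1.960).

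| ρ | s | V₁ | k | V | V/V₁ | Power |
|---|---|---|---|---|---|---|
| 0.3 | 8 | 329.6 | 4 | 281.6 | 0.854 | 85.8% |
| 0.3 | 8 | 329.6 | 16 | 269.6 | 0.818 | 87.3% |
| 0.3 | 10 | 401.6 | 4 | 326.6 | 0.813 | 87.5% |
| 0.3 | 10 | 401.6 | 16 | 307.9 | 0.767 | 89.3% |
| 0.5 | 8 | 272.0 | 4 | 224.0 | 0.824 | 87.0% |
| 0.5 | 8 | 272.0 | 16 | 212.0 | 0.779 | 88.8% |
| 0.5 | 10 | 344.0 | 4 | 269.0 | 0.782 | 88.7% |
| 0.5 | 10 | 344.0 | 16 | 250.3 | 0.727 | 90.8% |

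Variance falls by 15–27%, and power rises from 80% to about 86–91%.

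**3. What moves the result.**

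- Baseline also averaged over k readings: V = 2 × 144 × (1 − ρ) + 2s²/k. V/V₁ runs from 0.709 to 0.455 and power from 91.5% to 98.6%. This is an upper range, because it needs the same number of independent readings at both times.
- Month 6 only, with noise correlated 0.5 between readings in the window: s²/k becomes s² × (1 + 0.5(k − 1))/k. Power is then about 83–85%.
- Unequal counts: let w be the share of outcome variance that averaging can reduce. With 16 readings in the integrated arm and 1 in the other, power is 81.9% at w = 0.1 and 89.3% at w = 0.5. The gain shrinks but does not reverse.

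**4. Control status.** Take systolic BP alone, a true mean of 125 and s = 8 to 10 (assumed). A single reading exceeds 130 with probability 1 − Φ(5/s) = 27–31%. The mean of 4 independent readings does so with probability 1 − Φ(10/s) = 11–16%, and the mean of 16 with probability 1 − Φ(20/s) = 0.6–2.3%. The contrast is this large only near the threshold, and correlated readings reduce it.

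**The case against.** The strongest reply is that the quoted sentence is a fallback for participants without a 6-month value, and that a condensed article may leave the combination of several month-6 readings to a fuller document. This has some force: an averaging rule may exist elsewhere. But the article's own wording is singular throughout and its model has no participant-level term, so a reader who follows it would take one reading. The point concerns the method as stated.

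The second reply is that readings may be few. Sixteen a month is an ideal without a minimum. The Discussion accepts that participants may not measure, and Table 1 allows discharge once BP is at goal or well controlled. This stands, and it limits the gain.

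Four stronger readings are tempting, and the documents do not support them.

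- *The trial is underpowered or its sample size is wrong.* It is not; 660 reproduces exactly.
- *Power would rise to 89–95%.* That range follows from treating a single 6-month value as the outcome: (144 + s²/k)/(144 + s²) lies between 0.77 and 0.62. The outcome is change from baseline, and averaging month 6 alone leaves the baseline noise in place.
- *Averaging costs nothing.* No participants or visits are added, but automatic capture in the EHR is described only for the integrated arm. The article does not say that every self-reported reading reaches the data warehouse in usable form.
- *Averaging cures arm-dependent selection.* Dense automatic readings and sparse self-reported ones could make the chosen value differ by arm in timing or selection. A common window helps with timing, but a mean of selectively reported readings is still selected. Noise in a reading taken without selection costs precision and does not bias the mean difference.

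**Conclusion.** The concern holds as an avoidable loss of efficiency in the primary endpoint, and as misclassification near the threshold in the control status. It is neither an error in the sample size nor evidence of bias. Under the stated assumptions, averaging 4 to 16 month-6 readings takes power from 80% to about 86–91%. Averaging baseline as well gives more. Correlated readings (about 83–85% at correlation 0.5) or sparse ones give less. The direction does not depend on the assumed SDs; the size does, and the documents cannot settle it. The change is worth making before analysis, and the trial is not invalid without it.

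**What to change.** Define baseline home systolic BP and 6-month systolic BP each as the mean of all available home readings in a fixed, prespecified window (for example 14 to 28 days at month 6). Apply the same daily cap in both arms, for example the first two readings per day. Keep the baseline window short: the monitor arrives after randomisation, so a long window would take in early treatment effect. Derive control status from the month-6 means.

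Set no hard minimum count. If the window holds few readings, use those available. If it holds none, apply the existing closest-reading rule. A minimum would turn participants who now contribute into missing data, plausibly more often in the self-report arm.

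Report the number and timing of readings by arm, and add a sensitivity analysis weighted by reading count.

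The cost is a revised endpoint definition, a few lines of code and a check that self-reported readings reach the warehouse as structured data. No participants, visits or readings are added. The downside is that means from few readings are noisier, probably more often in the self-report arm, and selective self-report remains and should be stated as a limitation.

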## Methods

### Setting and Study Design

The University of California (UC) Health System is a large academic health system serving a diverse patient population throughout California, the United States, and internationally. It includes teaching hospitals, affiliations with community health clinics, health professional schools, research centers, and other health care entities. This study protocol describes a randomized, comparative effectiveness trial that will be conducted at 3 of the UC Health System sites (UC Davis [UCD], UC Los Angeles [UCLA], and UC San Francisco [UCSF]). Figure 1 describes the general timeline. Enrollment will occur over 6 months after study initiation, and each participant will be followed for 6 months after enrollment.

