Discharge from the program	BP at goal for 2 consecutive visits Resistant hypertension criteria Clinical concerns develop, for example, recurrent orthostatic symptoms with systolic BP <100 mm Hg, persistent changes in labs (electrolytes and GFR^f^), significant excursions in BP after confirming measurement technique, and unstable symptoms BP is above goal after 6 months The patient requests discharge	BP at goal for 2 consecutive visits Resistant hypertension criteria Clinical concerns develop, for example, recurrent orthostatic symptoms with systolic BP <100 mm Hg, persistent changes in labs (electrolytes and GFR), significant excursions in BP after confirming measurement technique, unstable symptoms BP is above goal after 6 months The patient requests discharge	BP is well controlled. Patient request or lost to follow-up. Complicating comorbid conditions develop
Site-specific inclusion criteria	None	The participant must be active on the web-based patient portal.	The participant must be active on the web-based patient portal.
Site-specific exclusion criteria (if any)	None	None	None

^a^BP: blood pressure.

^b^EHR: electronic health records.

^c^PCP: primary care physician.

^d^PMH: patient medical history.

^e^ASCVD: atherosclerotic cardiovascular disease.

^f^GFR: glomerular filtration rate.

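### A single reading from as early as month 2 can stand as the observed 6-month primary outcome, so participants whose readings stop between months 2 and 6 bypass the planned multiple imputation

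*Protocol article*

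**What the plan says.** The protocol article's Statistical Analysis section sets the primary comparison: linear mixed effects models will "compare changes from baseline home BP to 6 months from enrollment between the integrated and nonintegrated remote monitoring arms". Two sentences then deal with absent outcomes. For a patient with no BP at 6 months, "we will use the reading closest to 6 months, with a minimum 2-month period between the baseline and final reading". Directly after: "Missing data will be handled through multiple imputations using pattern-mixture models". The article does not state how the two rules are ordered. On the natural reading, substitution comes first and imputation takes what is left. The same section says: "A significance level of .05 will be used, and all analyses will follow the intention-to-treat principle".

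Four other places bear on which reading ends up being used:

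- Table 1 (Site-Specific Hypertension Interventions) lists reasons for leaving the site program. At UC Davis and UCLA one is "BP at goal for 2 consecutive visits", and at UCSF one is well-controlled BP. Other reasons are resistant hypertension and clinical concerns (UC Davis, UCLA), complicating comorbidity (UCSF) and the patient's request.
- The same table sets no minimum number of readings per month, only an ideal of 16.
- The section on BP monitors and EHR integration has integrated readings reach the record automatically, while control participants report theirs through the portal.
- Setting and Study Design says that "each participant will be followed for 6 months after enrollment", and Ethical Considerations says that BP is drawn from the EHR during the study period.

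**The concern.** The rule is single-value substitution across a gap of up to four months. The substituted number enters the model as if it had been measured at month 6.

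Two things follow. First, the people for whom a not-at-random method matters most, those whose readings stop part-way, are the ones the rule removes from its scope. Second, the choice of value is not neutral. A reading taken when someone has just been at goal twice is partly low by chance and tends to understate that person's later BP. A reading taken at discharge for resistant hypertension may err the other way. With automatic upload in one arm and self-report in the other, the share of carried values and their timing can differ by arm. That is how an error within arms becomes an error in the randomised contrast.

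At stake is the primary estimate. The controlled/uncontrolled secondary outcome is exposed too, if it is built from the same final reading.

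**Working it through.** **The plan's own figure.** The sample size is planned "to achieve an 80% power to detect a difference of 0.23 SDs and an anticipated 10% attrition rate". With a two-sided .05 level (sidedness is assumed), n per arm = 2(1.960 + 0.842)² / 0.23² = 297. Dividing by 0.90 gives 330 per arm, or 660 in total, as stated. The sample size is not at issue. The target of 0.23 SD equals 2.76, 3.45 or 4.14 mm Hg at assumed SDs of 12, 15 or 18; the article gives no SD in mm Hg.

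**Size of the bias.** Let p be the share of an arm whose final value is carried from before month 6, and e the mean of (carried value − true month-6 value) in that share. Then

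bias in (integrated − control) = p_I·e_I − p_C·e_C.

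A positive result counts against the integrated arm.

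*First set of assumptions (none from the article):* monthly visits, mean SBP 138, between-person SD 12, visit SD 8, a fall of 4 mm Hg over 3 months, discharge after two consecutive values below 130, and a stated share of discharged participants who then have no further readings. In simulation (300,000 per arm), 40% are discharged at goal before month 6, or 49% in an arm with an added 3.5 mm Hg effect.

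| Scenario | Formula | Simulated bias (mm Hg) |
|---|---|---|
| No effect; all discharged stop, both arms | 0.40(−3.27) − 0.40(−3.30) | +0.01 |
| True effect 3.5; all discharged stop, both arms | 0.49(−2.20) − 0.40(−3.27) | +0.22 |
| No effect; 10% vs 50% stop | 0.04(−3.40) − 0.20(−3.25) | +0.51 |
| No effect; 20% vs 80% stop | 0.08(−3.13) − 0.32(−3.22) | +0.76 |
| As above, with BP rebounding 5 after discharge | 0.08(−8.15) − 0.32(−8.25) | +1.96 |

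The formula gives +0.01, +0.23, +0.51, +0.78 and +1.99, which agrees with the simulation. With no true effect the arms are exchangeable, so swapping which arm stops more reverses the sign.

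*Second set (also assumed):* no true effect, SBP 142 falling 8 by month 3, between-person SD 12, within-person SD 8–10, goal 130 or 140, monthly visits, readings available at 95% of integrated and 50% of control visits before discharge. Only what happens after discharge is varied.

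| After discharge | Bias in contrast (mm Hg) |
|---|---|
| No readings in either arm | −0.3 to −1.1 |
| Each arm keeps its own rate | −0.04 to −0.12 |
| 80% integrated vs 20% control | +0.05 to +0.26 |
| Integrated continues, control stops | +0.36 to +0.69 |

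The sign turns on one quantity that the article does not give: whose readings continue after discharge.

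**Scope of the imputation.** A participant with any reading at least 2 months after baseline has a usable outcome under the rule. Imputation of the outcome is left with those who have none. Missing baseline BP or covariates would still be imputed.

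**The case against.** The strongest defence is that discharge is from the site program, not from the study. Follow-up runs 6 months for everyone, analysis is by intention to treat, BP comes from the EHR, monitors are mailed to participants' homes and nothing says they are returned. If readings continue, few participants need the rule. In the second set of assumptions, when each arm keeps its own reading rate, only about 5% of integrated values come from before month 6. Window width and the order of the two rules could also be settled in an analysis plan that is not shown.

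Most of this stands as a limit on size. It does not remove the point, because the article itself fixes a rule that reaches back to month 2.

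Three stronger readings are tempting and are not supported:

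- *That the rule carries forward at-goal discharge values as a matter of course.* No section says that readings stop at discharge, and some discharge reasons need not go with a low BP. The 40–70% of final values from before month 6 seen in simulation arises only if nobody has a reading after discharge.
- *That the integrated arm gains.* The sign reverses under equally plausible assumptions. Understating month-6 BP within arms (0.6–1.7 mm Hg with no post-discharge readings and 95% availability) is not bias between arms.
- *That imputation has almost nothing to do.* The 0–3% left without an outcome reading comes from a model with no attrition, whereas the article anticipates 10%.

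**Conclusion.** The point holds as a weakness in how the primary outcome is defined. A single value from as early as month 2 can count as an observed 6-month result, and participants whose readings stop between months 2 and 6 fall outside the planned imputation. The outcome-related discharge reasons, the absence of a minimum reading frequency and the different capture in the two arms make dependence on outcome and arm plausible; they do not establish it.

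Bias in the contrast is about zero if stopping is equal and there is no true effect, and 0.1–0.3 mm Hg if stopping is equal with a true effect of 3.5. It reaches roughly 1 mm Hg when stopping or reading availability differs by arm, and about 2 mm Hg if BP is also assumed to rebound by 5 after discharge. Against 3.45 mm Hg (SD 15 assumed), 1.1 is 32% and 1.96 is 57%. Direction and frequency cannot be known from the article, so no argument from the sign of the bias could later defend the result.

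**What to change.** Define the primary outcome from readings in a fixed window around 6 months, for example ±4 weeks, and draw EHR blood pressures for every randomised participant whatever their program discharge status. The discharge criteria themselves need no change.

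Treat anyone with no reading in the window as missing. Handle them with the planned multiple imputation, or with a longitudinal mixed model, using all earlier readings and discharge status. State that order explicitly. Keep the closest-reading rule as a sensitivity analysis, and report the timing of the final reading by arm.

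This should be written down before the blinded evaluation team sees outcomes by arm. The cost is analysis wording, a higher imputed fraction and a slightly wider confidence interval; the sample size is unaffected.
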